#### Cohort A

For each treatment, we will create a cohort of patients who are diagnosed with the condition the treatment is used for or ‘at risk’ of that condition. This will be determined by the indications and test results described in table 2. We will split each cohort into ‘exposed’ and ‘unexposed’ groups. The ‘exposed’ group will consist of patients who received a treatment of interest within 6 months of initial diagnosis of the condition for which the treatment is being given (the ‘indication’ for treatment). The ‘unexposed’ group will consist of all others in the cohort. Patients will be identified as having received a treatment of interest by product codes (see online supplementary files 1–3). Therefore, in this analysis, we will compare an ‘exposed’ group of individuals who were prescribed the treatment to an ‘unexposed’ group of individuals who received similar test results (ie, were ‘at risk’ of or diagnosed with the indication for treatment), but did not receive the treatment, as illustrated in figure 1. The aim of this approach is to address confounding by indication that could cause bias if the ‘unexposed’ group is drawn from the full population, whom are likely to be healthier. It will also allow us to minimise excluded immortal time bias as patients will be followed from a consistent index date (date first at risk or date of first diagnosis of the condition itself if there was no preceding period at risk).

**Table 2 BMJOPEN2016012044TB2:** The cohorts of type A, one for each treatment of interest

Cohort	Entry criteria
Treatments for hypertension	Patients who are ‘at risk’ of hypertension as indicated by one of the following: Medical code indicating a diagnosis of ‘at risk’ of hypertension. Recorded systolic blood pressure test result between 120 and 139 mm Hg. Recorded diastolic blood pressure test result between 80 and 89 mm Hg. In the case of no period ‘at risk’, patients who have hypertension as indicated by one of the following: Medical code indicating a diagnosis of hypertension. Product code indicating treatment for hypertension. Recorded systolic blood pressure test result of 140 mm Hg or more. Recorded diastolic blood pressure test result of 90 mm Hg or more. See online supplementary file 1 for code lists relating to hypertension.
Treatments for hypercholesterolaemia	Patients who are ‘at risk’ of hypercholesterolaemia as indicated by one of the following: Medical code indicating a diagnosis of ‘at risk’ of hypercholesterolaemia. Recorded test result where total cholesterol level is between 4 and 5 mmol/L. Recorded test result where LDL cholesterol level is between 2 and 3 mmol/L. In the case of no period ‘at risk’, patients who have hypercholesterolaemia as indicated by one of the following: Medical code indicating a diagnosis of hypercholesterolaemia. Product code indicating treatment for hypercholesterolaemia. Recorded test result where total cholesterol level exceeds 5 mmol/L. Recorded test result where LDL cholesterol level exceeds 3 mmol/L. See online supplementary file 2 for code lists relating to hypercholesterolaemia.
Treatments for type 2 diabetes	Patients who are ‘at risk’ of type 2 diabetes as indicated by a medical code. In the case of no period ‘at risk’, patients who have type 2 diabetes as indicated by one of the following: Medical code indicating a diagnosis of type 2 diabetes. Product code indicating treatment for type 2 diabetes. Medical code indicating a diagnosis of unspecified diabetes, first received over the age of 40. Product code indicating treatment with insulin, first received over the age of 40. This assumes that patients treated with insulin or receiving a diagnosis of unspecified diabetes after the age of 40 have type 2 diabetes. Patients with a recorded diagnosis of type 1 diabetes at any age will be excluded. See online supplementary file 3 for code lists relating to type 2 diabetes.

LDL, low density lipoprotein.

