Start of follow-up (index date)	Date at first risk of the condition the treatment is used for or date of first diagnosis of the condition itself if there was no preceding period ‘at risk’.	Date of first prescription of a treatment of interest.	Date of first diagnosis of neurodegenerative disease of interest.
Outcome	Diagnosis of neurodegenerative disease of interest.	Diagnosis of neurodegenerative disease of interest.	Death.
Exclusion criteria	Individuals with <12 consecutive months of records prior to cohort entry.	Individuals prescribed treatment and control medications at the same time or with <12 consecutive months of records prior to cohort entry.	Individuals with <12 consecutive months of records prior to cohort entry.
Statistical analysis	Conventional regression, propensity score regression, instrumental variable analysis and marginal structural models.	Conventional regression, propensity score regression, instrumental variable analysis and marginal structural models.	Conventional regression, propensity score regression and marginal structural models.

AD, Alzheimer's disease; ALS, amyotrophic lateral sclerosis; NADD, Non-Alzheimer's disease dementias; PD, Parkinson's disease.

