**Figure 1 BMJOPEN2016012044F1:**
[figure not shown]
The cohort construction for cohort type A, designed to eliminate immortal time bias. A patient will enter the cohort for a given treatment when they first become ‘at risk’ of the condition the treatment is used for or, in the case of no period ‘at risk’, when they are first diagnosed with the condition (see table 2). For example, when they are diagnosed as at ‘at risk of’ hypertension or, in the case of no period ‘at risk’, when they receive a diagnosis of hypertension. We define cohort entry in this way to avoid excluded immortal time bias that can occur when cohort entry is determined by treatment variation over time.^33^
^34^ Immortal time is the period during follow-up when the outcome cannot occur. Consider the hypertension example above, suppose we started following the treated patients in our cohort from the date of their first prescription of a treatment for hypertension and the untreated patients from a matched date. This would make it impossible for the treated patients to have an outcome, such as dementia, prior to their first prescription. Consequently, patients in this group would all have a period before treatment, when they could not be diagnosed with dementia, that is, they could not experience the outcome. This period is their immortal time, and it must be correctly attributed to the ‘unexposed’ group so that their outcome is not falsely attributed to their exposure. To do this, patients in the ‘exposed’ and ‘unexposed’ groups must be followed-up and compared from the same start date. In this cohort, we are minimising excluded immortal time by following patients from either a test result or diagnosis where possible. In order to capture all relevant patients, we will allow those receiving treatment without a recorded diagnosis to be included as it is assumed treatment suggests a diagnosis.

10.1136/bmjopen-2016-012044.supp1supplementary file

10.1136/bmjopen-2016-012044.supp2supplementary file

10.1136/bmjopen-2016-012044.supp3supplementary file

Follow-up for cohort A will start on the first date a patient is diagnosed with the condition the treatment is used for or ‘at risk’ of that condition (see table 2 and online supplementary files 1–3.) Follow-up will end with the earliest of a relevant neurodegenerative disease diagnosis, death or censoring due to the end of registration at a CPRD general practice.

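### Cohort A starts follow-up at the 'at risk' date but decides exposure by treatment after a possibly later diagnosis, so the Cox and propensity-matched analyses contain immortal time bias towards protection

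*Protocol article*

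**What the plan says.** **Time zero.** Table 1 starts cohort A follow-up at "Date at first risk of the condition the treatment is used for or date of first diagnosis of the condition itself", the second applying only where no 'at risk' period came before. Table 2 lets a patient enter the hypertension cohort on a "Recorded systolic blood pressure test result between 120 and 139 mm Hg", which is below the 140 mm Hg that marks hypertension itself.

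**Exposure.** In the Cohort A section, the exposed "group will consist of patients who received a treatment of interest within 6 months of initial diagnosis of the condition". The unexposed "group will consist of all others in the cohort". The 6-month window runs from diagnosis, not from time zero.

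**End of follow-up.** "Follow-up will end with the earliest of a relevant neurodegenerative disease diagnosis, death or censoring due to the end of registration" at the practice. No landmark is set.

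**Claims about immortal time.** The Figure 1 legend describes the construction as "designed to eliminate immortal time bias". Of the time before treatment it says "This period is their immortal time, and it must be correctly attributed to the" unexposed group. The means it gives is a shared start date. The Bias section adds that misclassified immortal time is prevented by taking exposure from the first prescription and analysing by intention to treat.

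**The concern.** In a randomised trial the group is known at time zero, so an intention-to-treat label is harmless. In cohort A the label depends on two later events, diagnosis and prompt treatment, which may come long after entry. Anyone whose follow-up ends first, through a neurodegenerative diagnosis, death or leaving the practice, falls into the unexposed group by definition. Early outcomes are therefore pushed into that group, while the exposed group is credited with time in which it could not have had an outcome.

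A shared start date cures *excluded* immortal time, the problem that the Figure 1 legend describes. Combined with a label fixed from that date, it turns the same time into *misclassified* immortal time, which the Bias section says is prevented.

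The Introduction says the findings will be used to prioritise drugs for trials, and cohort A is the only treated-versus-untreated comparison for incidence. A bias that favours treatment for all three drug groups bears directly on that use.

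**Working it through.** **1. What follows from the text alone.** Let E be the end of follow-up and R the time of first treatment, both measured from the cohort A index date. The rules above class a patient as exposed only if R < E. From 0 to R an exposed patient cannot have the outcome. By route of entry:

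- 'at risk' entry: R is the gap to diagnosis plus up to 6 months, with no upper limit on the gap;
- entry at diagnosis: R is at most 6 months;
- entry by a treatment code: R = 0, so no immortal time.

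**2. Direction.** Suppose treatment has no effect and the outcome rate is a constant λ. Let P1 and P0 be the person-time labelled exposed and unexposed, and I the pre-treatment time inside P1. All events occurring in I belong to patients labelled unexposed, so

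rate ratio = [λ(P1 − I)/P1] ÷ [λ(P0 + I)/P0] = (1 − I/P1) ÷ (1 + I/P0).

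This is below 1 whenever I > 0.

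**3. Size.** The protocol has no figure to reproduce: Table 3 covers cohorts B and C, and the Study size section says cohort A is difficult to size. The following inputs are assumptions, not protocol figures: outcome 0.005 per year, death 0.02 per year, deregistration 0.10 per year (0.05 in a variant), 60% of 'at risk' patients eventually diagnosed, 60% of the diagnosed treated evenly over the next 6 months, exponential gap to diagnosis, true HR 1, and 1,000,000 patients per scenario.

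| Entry | Mean gap (years) | Deregistration per year | HR, fixed label | HR, time split at treatment |
|---|---|---|---|---|
| All 'at risk' | 1 | 0.10 | 0.83 | 1.01 |
| All 'at risk' | 2 | 0.10 | 0.74 | 0.99 |
| All 'at risk' | 5 | 0.10 | 0.61 | 0.99 |
| All 'at risk' | 10 | 0.10 | 0.56 | 1.00 |
| All 'at risk' | 1 | 0.05 | 0.89 | 1.01 |
| All 'at risk' | 2 | 0.05 | 0.81 | 1.00 |
| All 'at risk' | 5 | 0.05 | 0.70 | 1.00 |
| Half at diagnosis | 2 | 0.10 | 0.87 | 1.02 |
| Half at diagnosis | 5 | 0.10 | 0.80 | 1.00 |
| Half at diagnosis | 5 | 0.05 | 0.85 | 1.01 |
| All at diagnosis (50% treated) | 0 | 0.10 | 0.94 | 1.00 |

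**4. Hand check of one row** (all 'at risk', 2 years, deregistration 0.10). Mean follow-up is 1/(0.005 + 0.02 + 0.10) = 8.0 years. The simulation has 27.9% exposed, with mean pre-treatment time 1.856 years, which is 18.8% of exposed person-time. Per patient, I = 0.279 × 1.856 = 0.518, P1 = 0.518/0.188 = 2.75 and P0 = 8.0 − 2.75 = 5.25. The formula gives (1 − 0.188)/(1 + 0.518/5.25) = 0.812/1.099 = 0.74, as in the table.

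**5. Yardstick.** Table 3 gives minimum detectable HRs of 0.844 to 0.968 for cohort B. Those are for other comparisons, but they show that artefacts of the size above are no smaller than effects the study regards as detectable.

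**The case against.** **The planned methods differ, so disagreement between them would expose the problem.** This stands in part. A reader might infer that the instrumental variable analysis shares the bias because it uses the same exposure. The documents do not support that. The instrument is what the physician prescribed to earlier patients, not this patient's survival to treatment. In a null simulation with 30% diagnosed at entry and a mean 2-year gap for the rest (outcome 1% and death 2% per year, instrument independent of the outcome and fixed at index), the fixed-label rate ratio was 0.66 and the naive 48-month risk difference −0.0187, but the instrumental variable risk difference was 0.0004 (SE 0.0005). The protocol does not say how the instrument is dated for untreated patients, so this is a possibility and not an assurance. Cox and propensity matching do share the fixed exposure, so agreement between those two reassures nobody.

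**Marginal structural models are planned for cohort A.** With time-varying treatment they could place pre-treatment time correctly, and the authors undertake to report every analysis. But the Statistical methods section makes their use for switching a secondary analysis. They lessen the problem without curing the primary one.

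**The protocol never says that pre-treatment time is exposed.** True. The Exposures section's rule about ignoring later events concerns stopping and switching, and the legend says the opposite. The conflict arises because no person-time split or landmark is stated that would honour the legend. The Cox section's reference to actual prescriptions does not supply one.

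**Treatment first recorded after the neurodegenerative diagnosis might still count.** In the simulations that brings the HR to 0.97–1.02. Nothing in the protocol says so, and exposure would then be defined after the outcome.

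**Elsewhere the text says minimise, not eliminate.** It does, in the Cohort A and Bias sections, but softer wording does not move the person-time.

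**Conclusion.** The point holds for the Cox and propensity-matched analyses of cohort A. The presence of the bias and its direction, towards protection, follow from the stated index date, exposure rule and fixed label.

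Its size does not follow from the documents. It depends on the gap between 'at risk' entry and diagnosis, the share entering at diagnosis or by treatment code, and length of registration. About 0.6 to 0.9 is a fair illustrative range when all enter 'at risk'. It is 0.80–0.87 if half enter at diagnosis and about 0.94 if all do. A separate null simulation with an outcome rate doubling every 5 years gave 0.60–0.89. A reader might infer that null HRs near 0.5 should be expected. A value of 0.49 does arise at constant hazard, but only with nobody entering at diagnosis and a mean 5-year wait, whereas Table 2 allows direct entry. The three cohorts may also differ, since 'at risk' of diabetes is identified by medical code alone.

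This should be corrected before analysis.

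**What to change.** 1. **Primary Cox analysis, cohort A:** treat exposure as time-dependent from the existing index date, with each patient unexposed until the first prescription.
2. **Propensity-matched analysis,** which needs a fixed exposure: set the index at diagnosis of the condition, classify by treatment in the next 6 months, start follow-up for both groups at that 6-month landmark, and measure covariates up to the landmark.
3. **Text:** align the Cohort A, Figure 1 legend, Exposures and Bias passages, and withdraw the statement that the present construction eliminates immortal time bias.

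**Cost.** The data are the same; the work is rewording and reprogramming. The landmark analysis loses events in the first 6 months and the 'at risk' patients who are never diagnosed, who are part of the intended comparator. Some of its covariates may be recorded after treatment has begun, so the Bias section's rule on covariate timing needs rewording. The time-dependent Cox analysis keeps everyone, but with covariates fixed at the index date it leaves time-dependent confounding to the marginal structural models.

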### Variables

#### Exposures

For our primary analysis, we will define all exposures based on the first prescription observed in the database.^10^ This is so that the target parameter estimated in the observational study will be comparable to that estimated by a randomised controlled trial (RCT). Analogous to an intention-to-treat analysis in a RCT, patients initially prescribed an active treatment medication (exposed), but later stop that medication or switch to a control drug (unexposed), will be allocated to treatment (ie, classified as exposed, irrespective of what happens in the future) and vice versa. First time prescriptions of the medications of interest (treatment and control) will be defined as people who received at least one prescription of the product but who had no use of a related product during the 12 months before the start of follow-up. The prescriptions will be identified using product codes recorded in the therapy file in the CPRD, which details the date each prescription was issued, the quantity of drug prescribed and the dosage. Patients initially receiving more than one prescription of a drug of interest will be included in our analysis in a group representing the specific combination of drugs they receive. The effects of treatment switching and disease control will be explored using marginal structural models. We will also consider disease severity for the treatment indications through the use of instrumental variable analysis.

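### Cohort A's 6-month exposure rule places patients first treated later in the unexposed group for all follow-up, contradicting the protocol's own description of that group and its first-prescription rule

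*Protocol article*

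**What the plan says.** The protocol article describes cohort A's exposure in three ways.

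- **Classification rule (Cohort A).** The exposed are those who "received a treatment of interest within 6 months of initial diagnosis of the condition for which the treatment is being given". The unexposed "group will consist of all others in the cohort".
- **Description of the contrast (Cohort A, same paragraph).** The comparison group had similar test results "but did not receive the treatment, as illustrated in figure 1". Sample selection and the Purpose row of Table 1 likewise speak of treated and untreated individuals.
- **General exposure rule (Exposures).** For the primary analysis, "we will define all exposures based on the first prescription observed in the database". No time window is mentioned.

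Follow-up in cohort A starts when the patient is first at risk of the condition, or at first diagnosis if there was no at-risk period (Table 1; Cohort A; Figure 1 legend).

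Table 2 lists what marks the condition when there was no at-risk period. For hypertension, one sufficient criterion is "Recorded systolic blood pressure test result of 140 mm Hg or more"; for hypercholesterolaemia, "Recorded test result where total cholesterol level exceeds 5 mmol/L". Type 2 diabetes is set by medical or product codes only, and its at-risk criterion reads "Patients who are ‘at risk’ of type 2 diabetes as indicated by a medical code".

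**The concern.** A patient whose first prescription comes more than 6 months after diagnosis is treated, yet sits in the unexposed group throughout. Under the description in the same paragraph that patient does not belong there, and under the Exposures section the patient is exposed. Two analysts following different sentences would build different cohorts.

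Cohort A is the protocol's only treated-versus-untreated comparison for incidence. If its controls include people taking the drug under study, the HR does not estimate the contrast the protocol names. The Study size section gives no detectable HR for cohort A, so its statement that power is more than adequate makes no visible allowance for this loss.

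**Working it through.** **No figure to reproduce.** The protocol states no event count, power or HR for cohort A. Table 3 covers cohorts B and C only.

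**Step 1: apply the rules to two illustrative patients, each followed for 120 months.**

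| | Patient 1 | Patient 2 |
|---|---|---|
| Follow-up starts | Month 0 (diagnosis, no at-risk period) | Month 0 (at risk) |
| Diagnosis | Month 0 | Month 60 |
| First prescription | Month 7 | Month 63 |
| Cohort A rule | Unexposed for 120 months | Exposed for 120 months |
| Received the treatment? | Yes | Yes |
| First-prescription rule | Exposed | Exposed |
| Time under the wrong label | 120 − 7 = 113 treated months counted as unexposed | 63 untreated months counted as exposed |

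Patient 1 shows the contradiction. Patient 2 shows an opposite problem: the first 63 months must be free of the outcome for the patient to be classed as exposed at all.

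**Step 2: effect of late starters alone.** Let f be the treated share of unexposed person-time. The protocol does not give it, so 0.1 to 0.5 is assumed. With a constant hazard ratio,

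observed HR = HR / (1 − f + f × HR), and events needed rise by (ln HR / ln observed HR)².

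For HR 0.80 and f = 0.3: 0.80 / (0.70 + 0.24) = 0.851, and (ln 0.80 / ln 0.851)² is about 1.9.

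| f (assumed) | True HR 0.80 seen as | True HR 0.90 seen as | Events needed, multiple |
|---|---|---|---|
| 0.1 | 0.816 | 0.909 | about 1.2 |
| 0.2 | 0.833 | 0.918 | about 1.5 |
| 0.3 | 0.851 | 0.928 | 1.9–2.0 |
| 0.5 | 0.889 | 0.947 | 3.6–3.8 |

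**Step 3: add the documented start of follow-up.** A cohort of 60,000 was simulated three times per scenario, with unadjusted Cox models and the cohort A rule. Assumptions: outcome hazard 1% per year, 15 years' follow-up, 5% per year censoring, 30% treated within 6 months of diagnosis and, where there is an at-risk period, a mean of 5 years from at risk to diagnosis.

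| Scenario | True HR 0.80 seen as | True HR 1.00 seen as |
|---|---|---|
| All enter at diagnosis, no late starts | 0.75–0.80 | 0.94–0.98 |
| All enter at diagnosis, late starts 10%/year (f about 0.40) | 0.82–0.84 | 0.95–0.96 |
| All enter at diagnosis, late starts 20%/year (f about 0.58) | 0.89–0.92 | 0.95–0.99 |
| 50% enter at risk, late starts 10%/year | 0.64–0.68 | 0.72–0.79 |
| 80% enter at risk, late starts 10%/year | 0.55–0.59 | 0.67–0.72 |

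When everyone enters at diagnosis, late starts dilute the effect as step 2 predicts. The values fall a little below the formula (0.80 / 0.92 = 0.870 at f = 0.40), which is expected because up to 6 months of untreated time still counts as exposed. Once many patients enter at risk, the untreated time credited to the exposed outweighs the dilution, and a drug with no effect appears protective. The inputs are assumed, so the table shows direction only.

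**Step 4: when does the 6-month clock start?** The Cohort A section says initial diagnosis. The Figure 1 legend has patients enter "when they are first diagnosed with the condition (see table 2"), which suggests that a single raised reading counts as diagnosis for hypertension and hypercholesterolaemia. If so, more patients would be late starters. The misclassification does not depend on this: with a coded diagnosis as the start, anyone first treated after 6 months is still unexposed, in all three drug groups.

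**The case against.** The strongest defence is that a fixed initiation window, with later starters kept in the unexposed group, is a recognisable intention-to-treat contrast: early initiation versus none. The Exposures section says the allocation principle also applies in reverse, and the protocol assigns switching and time-dependent confounding to marginal structural models, which Table 1 lists for cohort A. On this view some dilution belongs to the target, and the Cohort A rule is simply the local form of the general one.

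Part of this stands. Early initiation would be a legitimate estimand, and some dilution would come with it. But the protocol never states that estimand; it names treated versus untreated. The reverse clause is attached to patients who began on a control drug, and cohort A has none. The marginal structural models are secondary for switching and do not correct the primary Cox, propensity or instrumental variable contrasts.

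Two further objections stand in full. The single-test clock is an inference: Table 2 lists entry criteria, its raised-reading criteria apply only where there was no at-risk period, and the Figure 1 sentence defines cohort entry, not the exposure window. It cannot apply to type 2 diabetes. Second, a reader might infer that the cohort A HR is diluted overall, so that any apparent benefit is conservative. The documents do not support that, because the at-risk start of follow-up pushes the other way and can dominate.

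**Conclusion.** The exposure definition for cohort A is wrong as written and needs to be changed. It contradicts the description in its own paragraph, the stated purpose of the cohort and the first-prescription rule, and it keeps treated patients among the controls for all follow-up.

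Considered alone, this mechanism moves a true HR of 0.80 to between 0.82 and 0.89 for an assumed 10% to 50% of unexposed person-time treated. The actual share cannot be derived from the protocol. Neither the size nor the sign of the net bias is known, since untreated, event-free time credited to the exposed works towards apparent benefit. The Figure 1 legend itself requires pre-treatment time to be attributed to the unexposed, and the fixed rule does not do this.

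**What to change.** Reconcile the Cohort A and Exposures sections as follows.

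- **Cox models.** Count person-time as unexposed until the first prescription of the treatment and as exposed from then on, whatever stopping or switching follows. This keeps the first-prescription principle and corrects both errors shown in step 1.
- **Propensity and instrumental variable analyses.** Where exposure must be fixed, start follow-up when exposure status is fixed and describe the contrast as early initiation versus no early initiation. The protocol would need to say what that date is for at-risk patients who are never diagnosed.
- **Reporting.** Give the number of late starters by drug group. Keep the present 6-month rule as a sensitivity analysis under the same early-initiation label.
- **Clock.** State whether a Table 2 test result counts as initial diagnosis.

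The cost is protocol wording and one time-varying exposure variable built from prescription dates already held. The main downside is that covariates are defined before the index date (Bias section), so they may miss confounding that arises between the index date and a later first prescription. The planned marginal structural models address this. If late starters were censored in any analysis, weights for that censoring would have to be added, because the Marginal structural models section plans treatment weights only.
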